**Methods:**

MARS-CA is conducted at a university outpatient training center for cognitive-behavior therapy. Short session-introducing interventions with mindfulness elements will be compared to short session-introducing relaxation interventions and no session-introducing intervention to explore their effects on symptomatic outcome and therapeutic alliance. The session-introducing interventions will take place at the beginning of 24 subsequent therapy sessions. We hypothesize that patients’ symptomatic outcome and therapeutic alliance improve more strongly in the mindfulness condition than in the other two conditions and that the mindfulness condition moderates the relationship between therapeutic alliance and symptomatic outcome. Patients and their trainee therapists will be randomized to one of the three treatment arms. Participants aged between 11 and 19 years and having a primary diagnosis of either a depressive disorder, an anxiety disorder, or a hyperkinetic disorder will be included. Therapeutic alliance will be assessed after every therapy session (therapy session 1 to therapy session 24), symptomatic outcome will be assessed before the start of treatment (pre), after the 3rd, the 10th, and the 17th therapy sessions, at the end of treatment (24th therapy session, post), and at a 6-month follow-up. Additionally, mindfulness and mindfulness-related measures as well as demographic data, adherence, allegiance, and therapeutic techniques will be assessed. It is our aim to assess a sample of 135 patients. We will conduct multilevel modeling to address the nested data structure.

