#### Sample size {14}

A recent meta-analysis has detected small to medium effects of MBIs in RCTs with youth in depression (*d* = 0.27), anxiety (*d* = 0.16), executive functions (*d* = 0.30), and attention (*d* = 0.19) [24]. A meta-analysis that has analyzed the effects of meditation in non-clinical groups of adult meditators has detected moderate effect sizes for meditation compared to relaxation (*r* = .21) on psychological outcomes [43].

Taking these results into account, power analyses with G*Power [44] for the detection of small to medium-sized effects (Cohen’s *f* = 0.12) for the interaction between time (pre, T3, T10, T17, T24) and treatment condition (IG-M vs. CG-R vs. CG) (analysis of variance (ANOVA) repeated measures, within-between-interaction, *α* = 0.05, power (1 − β) = 0.80, number of groups = 3, number of measurements = 5, pre–post correlation *r* = 0.5, nonsphericity correction = 1) for the YSR 11-18R total score primary outcome resulted in a sample size of 108 patients. Although this should only be seen as a proxy for the power of the reported multilevel models (MLMs), previous research showed that power in MLM is often comparable to (or even higher than) power in an ANOVA design [45, 46]. The planned sample size should, therefore, be considered a conservative estimate required to detect a small to medium sized condition × time interaction. Taking a drop-out-rate of about 25% into account (i.e., 27 patients), a total sample of 135 patients will be assigned to one of the three treatment groups by a stratified randomization process.

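### The 25% drop-out allowance is added to 108 rather than divided out: 135 patients leave about 101 completers, with power of about 0.77 rather than 0.80

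*Protocol article*

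**What the plan says.** The sample-size section bases the trial on a G*Power calculation "for the detection of small to medium-sized effects", with Cohen's f set at 0.12 for the interaction of time and condition on the YSR 11-18R total score. The test is an ANOVA described as "repeated measures, within-between-interaction", with alpha 0.05, power 0.80, "number of groups = 3, number of measurements = 5", a correlation of 0.5 and a nonsphericity correction of 1. The result is 108 patients. The section presents the ANOVA as a stand-in for the multilevel models and calls the resulting size conservative.

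The drop-out step follows: "Taking a drop-out-rate of about 25% into account (i.e., 27 patients), a total sample of 135 patients will be assigned". The Methods part of the abstract repeats the total: "It is our aim to assess a sample of 135 patients".

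Two other sections bear on this. The eligibility section counts as drop-out any patient who ends therapy before session 24. The section on non-adherence and missing data plans both an intention-to-treat and a completer analysis.

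**The concern.** A drop-out rate is a proportion of the patients who enter the trial. The plan takes 25% of the number it wants to retain and adds it on. This gives too few patients, because the 25% loss also falls on the patients added. The count in the parenthesis leaves no doubt about the method: 27 patients is a quarter of 108, but only a fifth of the 135 who are assigned.

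The section therefore makes three statements that do not fit together: 135 assigned, about 25% lost, and 80% power. Readers will use this section to judge how informative a null result on the primary outcome is. As written, it overstates either the loss the trial can absorb or the power left after that loss.

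**Working it through.** **Inputs**, all from the Sample size section: f = 0.12; groups k = 3; measurements m = 5; correlation r = 0.5; nonsphericity correction 1; alpha = 0.05; target power 0.80; required N = 108; drop-out about 25%, taken as 27; total 135. Equal allocation comes from the Sequence generation section.

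**Step 1: reproduce the plan's 108.** The G*Power model for a within-between interaction uses a noncentral F distribution with

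- λ = f² × N × m / (1 − r) = 0.0144 × N × 5 / 0.5 = 0.144 N
- df1 = (k − 1)(m − 1) = 2 × 4 = 8
- df2 = (N − k)(m − 1) = 4(N − 3)

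Power is the probability that this variable exceeds the 5% critical value of the central F.

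| N analysed | λ | df2 | Power |
|---|---|---|---|
| 107 | 15.41 | 416 | 0.803 |
| 108 | 15.55 | 420 | 0.808 |

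The smallest N that reaches 0.80 is 107, and the smallest multiple of three is 108. The plan's 108 is reproduced.

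**Step 2: reproduce the plan's 135.** 0.25 × 108 = 27, and 108 + 27 = 135. The total is reproduced only by adding 25% of 108.

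**Step 3: apply the drop-out rate to those randomised.**

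- Remaining from 135 at 25% loss: 135 × 0.75 = 101.25
- Needed to retain 108 at 25% loss: 108 / 0.75 = 144, or 48 per arm
- Loss at which 135 retains 108: 1 − 108/135 = 27/135 = 20%

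**Step 4: power at the number remaining**, same model.

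| N analysed | λ | df2 | Power |
|---|---|---|---|
| 101 | 14.54 | 392 | 0.775 |
| 102 | 14.69 | 396 | 0.780 |
| 108 | 15.55 | 420 | 0.808 |
| 135 (no loss) | 19.44 | 528 | 0.901 |

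The shortfall against 108 is 108 − 101 = 7 completers. In randomised patients it is 144 − 135 = 9. Power at 101 lies 0.025 below the target of 0.80 and 0.033 below the 0.808 that 108 patients give.

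**The case against.** The strongest reply is that 0.775 describes a completer ANOVA, which is not the only planned analysis. The plan specifies a multilevel model, includes an intention-to-treat analysis, and notes that multilevel power is often comparable to or higher than ANOVA power. A patient who leaves shortly before session 24 may already have given YSR scores at pre-treatment and at sessions 3, 10 and 17, which are four of the five measurements in the power calculation. With complete data on all 135 patients the same model gives 0.901. If partial data are kept, intention-to-treat power should lie somewhere between 0.775 and 0.901, and the document does not allow a closer figure. This stands: it has not been shown that intention-to-treat power is below 0.80.

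It does not rescue the sentence. The allowance is added to a number that assumes five measurements per patient, and the section does not cite partial data as a reason for a smaller allowance. A completer analysis is also planned, and there the early data of drop-outs do not count. The remark that the size is conservative compares ANOVA with multilevel power and does not address the drop-out step.

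It is also fair to say that the gap is small beside the uncertainty in the inputs. At N = 101, 80% power is reached with f = 0.123 instead of 0.12, or with a correlation of about 0.53 instead of 0.5. That limits the importance of the error but does not make the figures agree.

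Finally, the text does disclose the count of 27, and 108 + 27 = 135 is correct as a sum. What is wrong is calling 27 a 25% drop-out when 135 are randomised. The word for "approximately" before the percentage does not cover the difference, because the count fixes the rate at 20%.

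**Conclusion.** The concern holds. On the plan's stated calculation, 135 randomised patients with 25% drop-out leave about 101 completers and power of about 0.775, below the stated 0.80. The 135 is consistent with 80% power only at a drop-out of about 20%. The shortfall is 7 completers or 9 randomised patients.

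The power figure rests on the plan's own inputs and on drop-outs contributing nothing, as in a completer analysis. The intention-to-treat multilevel analysis will lose less, by an amount the document does not allow one to state. The design is not endangered, but the justification of the sample size is wrong as written and should be corrected.

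**What to change.** Keep 135 and correct the sentence in the Sample size section in one of two ways:

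- State that 135 randomised patients allow for a drop-out of 20%, which leaves 108 completers and the stated power.
- Keep the 25% rate, and state that about 101 completers are then expected, with power of about 0.77 for f = 0.12 in the completer calculation. A remark that the intention-to-treat multilevel analysis also uses the data of drop-outs up to the time they leave may be added.

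Retaining both 25% and 108 completers would mean randomising 144, but the correction does not require this. The cost is one sentence: the stated tolerance for drop-out, or the stated power, becomes slightly less favourable. The abstract gives only the total of 135 and needs no change.

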#### Recruitment {15}

The study will be conducted at the outpatient training center for child and adolescent cognitive behavior therapy (CBT) at the Center for Psychological Psychotherapy (CPP) Heidelberg. Approximately 60 trainee therapists treat around 500 patients under 18 years of age, and with different type of mental disorders, per year. More than half of the patients at the outpatient training center are diagnosed with either a depressive disorder, an anxiety disorder, or a hyperkinetic disorder and thus are eligible for MARS-CA. We are optimistic regarding the recruitment process as the trainee therapists and patients are used to research settings due to the university affiliation of the outpatient training center. Additionally, parts of the research team have already successfully completed a similar study with an adult patient sample [15].

### Assignment of interventions: allocation

#### Sequence generation {16a}

Participants in the study will start their therapy sessions either with a SIMI, a SIRI, or no intervention. Treatment allocation will be performed by a blocked and stratified randomization process with a computerized random number generator. Patients will be stratified according to their main diagnosis (hyperkinetic disorder, depression, or anxiety disorder) and then equally randomized into one of the three treatment arms by a balanced blocking procedure.

#### Concealment mechanism {16b}

Randomization lists are saved in a password-protected document on the server of the outpatient training center for children and adolescents of the University of Heidelberg. Only a research assistant of the institute that is not part of the MARS-CA research team has access to this document.

#### Implementation {16c}

Patients will be enrolled in the study by the trainee therapists and in consultation with one researcher of the MARS-CA team. Patients will be assigned to one of the three intervention arms by an independent research assistant who is not part of MARS-CA research team.

### Assignment of interventions: blinding

#### Who will be blinded {17a}

The focus of the current study is on external validity and generalizability of the results to routine clinical practice. Consequently, according to extension of the CONSORT statement concerning the criteria of a pragmatic randomized controlled trial [47, 48], in the current study, no blinding will be implemented.

#### Procedure for unblinding if needed {17b}

Not applicable, no blinding implemented.

### Data collection and management

#### Plans for assessment and collection of outcomes {18a}

MARS-CA trainee therapists who treat MARS-CA patients will conduct the session-introducing interventions and will collect the required outcomes at the appropriate measurement time points (for detailed information about the measurement time points, see Table 1). All MARS-CA therapists will be participating in two workshops on the study process conducted by the research team and prior to the study (workshops content: theoretical information about mindfulness and relaxation interventions, specific study procedure, self-experience of mindfulness exercises between the first and the second workshop). To obtain complete data, trainee therapists are routinely contacted by MARS-CA research assistants and reminded to fill in the required therapist questionnaires and to prompt their patients to do the same. All questionnaires of both therapists and patients are administered via the online platform SoSci Survey (www.soscisurvey.de; [49]) or via paper-pencil.

Primary outcome of the study is the psychopathological symptomatology of the patients. This is assessed by the Youth Self-Report 11-18R (YSR 11-18R; [42]) total score. The YSR 11-18R total score consists of 112 items, which are rated on a three-step scale. The measure shows internal consistencies of .68 ≤ α ≤ .85 for the problem subscales and .88 ≤ α ≤ .94 for second-order scales (external score, internal score, and total score). Convergent and discriminant validity of the YSR 11-18R has been explored with the English version of the YSR in a clinical Australian sample [50]. To the authors’ knowledge, no study has explored the validity of the YSR 11-18R in a German sample. The completion of the YSR 11-18R takes about 15–20 min.

Secondary outcome measures are therapeutic alliance, development of mindfulness, self-compassion, and empathy as well as depressive, anxiety, and hyperkinetic symptoms of the patients. Therapeutic alliance will be assessed by the German version of the Therapeutic Alliance Scale for Children (FTB-KJ; [51]). The FTB-KJ constitutes the session questionnaire, administered to both patients and therapists after every psychotherapy session with a duration of approximately 2 min. The FTB-KJ is a self-report instrument comprising the patient’s as well as the therapist’s perspective, consisting of 12 items rated on a four-step scale and demonstrating good internal consistency (*α* = .83 for the total score). Convergent validity has been demonstrated by significant positive correlations with other instruments to assess therapeutic alliance [51]. Symptom severity has significantly correlated with a poorer therapeutic alliance from the patient’s perspective, especially for boys. Patient and therapist perspective of the FTB-KJ are moderately correlated [51].

General development of mindfulness among patients and therapists across the course of the study will be assessed by the German versions of the “Kentucky Inventory of Mindfulness Skills” (KIMS-D) (therapists; [52]) and the Child and Adolescent Mindfulness Measure (CAMM) (patients; [53]). The KIMS-D consists of 39 items that are rated on a five-step scale and takes about 5 min to complete. Exploratory factor analysis has revealed excellent internal consistencies (.83 ≤ α ≤ .91). Satisfactory convergent and discriminant validity of the KIMS has been demonstrated by significant associations with personality, life satisfaction, and psychopathology questionnaire [52]. The CAMM [53] is based on the KIMS [54] and is intended for youths over the age of 9 years. The measure includes ten items, rated on a five-step scale, with a good internal consistency of *α* = .80. It takes about 3 min to complete. The CAMM has showed significant associations with quality of life, academic competence, and social skills, as well as significant negative associations with somatic complaints, internal, and external psychopathology [53].

Patients’ and therapists’ general development of self-compassion across the course of the study is assessed by the German version of the “Self-Compassion Scale” (SCS-D) (therapists; [55]) and an adapted version of the SCS for Children (patients; [56]). The SCS-D consists of six subscales with 26 items in total and takes about 5 min to complete. Items are rated on a five-step scale. Internal consistency for the total SCS-D scale is *α* = .91. Retest reliability ranges between .72 and .92 [55]. Construct and criterion validity have been shown by positive associations with subjective well-being and negative associations with symptom distress [55]. The SCS for children also consists of 26 items, takes about 5 min to complete, and is rated on a five-step scale. It shows poor to almost excellent internal consistencies with .54 ≤ α ≤ .87 [56]. Construct validity has been given by a positive association between self-criticism and the negative subscales of the SCS for children as well as by a positive association between self-esteem and the positive subscales of the SCS for children [56].

Therapists’ general development of empathy is assessed by the Empathy Scale for Social Workers (ESSW; [57]), adapted for psychotherapists. The ESSW consists of 41 items, rated on a five-step scale, and takes about 5 min to complete. The questionnaire has shown an internal consistency of *α* = .83. Convergent and discriminant validities have been shown by significant positive associations to other empathy scales and a significant negative association with a verbal aggressiveness scale [57].

Patients’ hyperkinetic disorder symptoms are assessed by the problem scales of the ADHD self-rating scale of the Diagnostic System for Mental Disorders in Childhood and Adolescence (DISYPS-III), (SBB-ADHS; [58]), consisting of 20 items rated on a four-step scale, and taking about 5 min to complete. Internal consistency for the total score is *α* = .88. To the authors’ knowledge, no study has explored the validity of the DISYPS-III, SBB-ADHS.

Depressive symptoms of the patients are assessed by the problem scales of the depression self-rating scale of the DISYPS-III (SBB-DES; [58]). The problem scales of the SBB-DES consist of 29 items, rated on a four-step scale, take 5 min to complete, and show an internal consistency of *α* = .89. To the authors’ knowledge, no study has explored the validity of the DISYPS-III, SBB-DES.

Anxiety symptoms of the patients are assessed by the problem scales of the anxiety self-rating scale of the DISYPS-III (SBB-ANG; [58]). The problem scales of the SBB-ANG consist of 44 items, rated on a four-step scale, and take 5 min to complete. Total score consistency is *α* = .94. To the authors’ knowledge, no study has explored the validity of the DISYPS-III, SBB-ANG.

Additionally, demographic data, allegiance effects, and therapeutic techniques will be assessed. As a manipulation check, the Practice Quality-Mindfulness will be applied to patients (PQ-M; [59]). The six items of the PQ-M assess the perceived quality of mindfulness implementation operationalized as perseverance in (a) receptive and (b) present-moment attention. Duration of the questionnaire is about 2 min. The measure shows good psychometric properties with .72 ≤ α ≤ .87. A positive association to another mindfulness questionnaire has confirmed convergent validity. Criterion validity has been given by the predictive power of the PQ-M in relation to measures of life satisfaction and reduction of psychopathological symptoms. The instrument has been developed for adult patients and will be used in an adolescent sample in the present study.

Potential allegiance effects will be assessed by the Credibility/Expectancy Questionnaire (CEQ; [60]). The questionnaire addresses treatment expectancy and rationale credibility in clinical outcome studies. The measure has good psychometric properties with .79 ≤ α ≤ .90 for the subscales and takes about 2 min to complete. Construct validity has been confirmed for the expectancy factor, but not for the credibility factor [60]. It has been developed for adult patients and will be used in an adolescent sample in the present study.

Specific therapeutic techniques will be assessed by the Heidelberg Inventory of Cognitive-Behavioral Interventions (HICBI; [61]). The HICBI consists of 33 items and takes about 5 min to complete. Psychometric properties of the measure are limitedly acceptable to good with .59 ≤ α ≤ .82 and convergent validity is between -.01 ≤ r ≤ .26 for a therapist measure assessing general change. Criterion validity has not been confirmed.

Patients’ and therapists’ in-session therapeutic presence will be assessed by the Therapist Presence Inventory (TPI; [62]). This instrument measures in-session presence operationalized as being fully in the present moment with an attitude of acceptance and openness. Exploratory factor analysis (EFA) has revealed an excellent one-factor structure and good internal consistency with *α* = .75. Duration of the questionnaire is about 3 min. While construct validity is satisfactorily given, criterion validity is only sufficient for the patients’ version, not for the therapists’ version [62]. The instrument has been constructed for adult patients and will be used in an adolescent sample in the present study.

In sum, the completion of the therapists’ survey to each measurement time point takes about 20–25 min, the completion of the patients’ survey to each measurement time point takes about 45–50 min. Additionally, the administration of the session questionnaire after every therapy session takes about 2 min for both the therapist and the patient.

#### Plans to promote participant retention and complete follow-up {18b}

Retention of patients and assessment of data will be realized by close collaboration between trainee therapists and MARS-CA research assistants (via personal meetings, phone calls, and e-mail contact). Assessment of data (during active study participation and follow-up) can be executed either online via an online platform [49] or via paper pencil so that data collection is as convenient as possible for all study participants.

#### Data management {19}

All documents of MARS-CA will be stored at the outpatient training center for children and adolescents of the University of Heidelberg. Data of the study participants will be pseudonymized during active study phase and anonymized after study completion, using a unique study identifier code. With regard to electronic MARS- CA data, all electronic documents will be password-protected. Only MARS-CA staff will have access to them. Informed consent of trainee therapists, caregivers, and patients will be stored separately from other MARS-CA data in a locked cupboard in the MARS-CA research office. All MARS-CA data is stored on the web-based server of the outpatient training center for children and adolescents of the University of Heidelberg. Data of MARS-CA will be stored for at least 10 years after study completion.

#### Confidentiality {27}

All members of the MARS-CA research staff have been informed about data privacy and professional secrecy with regard to MARS-CA participants. Data management will be conducted in accordance to the Data Protection Act, 2018 and in accordance to the demands of the local ethics committee of the Faculty of Behavioral and Cultural Studies at the University of Heidelberg, Germany.

